### Study timeline

The W1 survey battery and the W1 PA monitoring will be included in data collection at W1. Participants will be asked to complete the W1 survey battery by week 1 (see the survey battery section for detailed information). Then, participants will be asked to complete the W1 PA monitoring by week 3 (see the PA monitoring section for detailed information). After W1, the 4-week access to the PAS intervention will be given to PAS participants by week 7. The W2 survey battery will be included in data collection at W2, but there will be no W2 PA monitoring based on the conceptual model of the PAS intervention. Participants will be asked to complete the W2 survey battery by week 8. The W3 survey battery and the W3 PA monitoring will be included in data collection at W3. Participants will be asked to complete the W3 survey battery by week 12. Then, participants will be asked to complete the W3 PA monitoring by week 14.

### Feasibility outcomes

The primary feasibility outcomes in the study will be: (a) participation rate (i.e., Aim 1), (b) engagement behavior (i.e., Aim 2), and (c) a preliminary effect size estimate for the direct effect of PAS to accelerometer-based assessment of PA (i.e., Aim 3). There will be secondary feasibility outcomes in Aim 1, 2, and 3. Threshold values for a traffic light system for each of the specific indicators that will be used to evaluate each aim are based on inferences drawn from the results of previous research [46, 47] and commonly used heuristics for Cohen’s *d* [48]. Data observed below a lower threshold (i.e., resembling red light) will suggest a potentially serious problem. Data observed above a lower threshold but below an upper threshold (i.e., resembling a yellow light) will suggest the need for caution. Data observed above an upper threshold (i.e., resembling green light) will suggest support for the feasibility of a future definitive Randomized Controlled Trial (RCT). The lower and upper bound threshold values for the traffic light system by aim are summarized in Table 2.

**Table 2 Tab2:** Lower and upper bound threshold values for the traffic light system by aim

Aim	Lower Bound Threshold	Upper Bound Threshold
Aim 1		
Recruitment rate	< 40%	≥ 60%
Eligibility rate	< 60%	≥ 80%
Consent rate	< 80%	≥ 90%
Participation rates	< 50%	≥ 70%
Retention rates	< 40%	≥ 60%
Aim 2		
Engagement behavior in the PAS intervention	< 40%	≥ 60%
Quantitative acceptability of the PAS intervention	< 60%	≥ 80%
Dichotomous acceptability of the PAS intervention	< 60%	≥ 80%
Qualitative acceptability of the PAS intervention	at least one potentially serious problem	absence of a potentially serious problem
Quantitative acceptability of accelerometer-based assessment of physical activity	< 60%	≥ 80%
Dichotomous acceptability of accelerometer-based assessment of physical activity	< 60%	≥ 80%
Qualitative acceptability of accelerometer-based assessment of physical activity	at least one potentially serious problem	absence of a potentially serious problem
Aim 3		
Intention-to-treat approach	< 0.00	≥ 0.20

*PAS* Physical Activity Self-efficacy

### Aim 1

The Aim 1 is to determine the feasibility of implementing the PAS intervention for adults with obesity. The participation rate will be the primary feasibility outcome in Aim 1. There will be secondary feasibility outcomes (e.g., recruitment rate) in Aim 1.

#### Recruitment rate

Recruitment rate will be defined as the percentage of patients who select “yes” when asked if they are interested in determining if they are eligible for participation in this study: (*n*_interested_/[*n*_interested_ + *n*_not interested_]) × 100. The lower bound threshold is < 40%. The upper bound threshold is ≥ 60%.

#### Eligibility rate

Eligibility rate will be defined as the percentage of interested patients who are presented with the informed consent form: (*n*_eligible_/*n*_interested_) × 100. The lower bound threshold is < 60%. The upper bound threshold is ≥ 80%.

#### Consent rate

Consent rate will be defined as the percentage of eligible patients who consent to participate in this study: (*n*_consent_/*n*_eligible_) × 100. The lower bound threshold is < 80%. The upper bound threshold is ≥ 90%.

#### Participation rate

Participation rate at wave W, where W = W1 or W2 or W3, will be defined as the percentage of consented patients who provide usable data (e.g., non-missing data) at wave W: (*n*_usable data at wave W_/*n*_consent_) × 100. The lower bound threshold is < 50%. The upper bound threshold is ≥ 70%.

#### Retention rate

Retention rate through wave W, where W = W2 or W3, will be defined as the percentage of consented patients who provide usable data (e.g., non-missing data) at W1 through wave W: (*n*_usable data through wave W_/*n*_consent_) × 100. The lower bound threshold is < 40%. The upper bound threshold is ≥ 60%.

### Aim 2

The Aim 2 is to determine the acceptability of implementing the PAS intervention for adults with obesity. The engagement behavior in the PAS intervention will be the primary feasibility outcome in Aim 2. There will be secondary feasibility outcomes (e.g., quantitative acceptability of the PAS intervention) in Aim 2.

### Engagement behavior in the PAS intervention

Engagement behavior at wave W, where W = W2, will be defined as the percentage of the number of post-introductory challenges completed in the PAS intervention at wave W: (*n*_post-introductory challenges completed W_/*n*_post-introductory challenges available_) × 100. The percentage will be used to assess the extent of usage in the PAS intervention. The lower bound threshold is < 40%. The upper bound threshold is ≥ 60%.

### Quantitative acceptability of the PAS intervention

Percentage of responses observed in “agree” or “strongly agree” to each of the 14 Likert-scale items designed to assess a subjective experience of the PAS intervention will be calculated at wave W, where W = W2. The lower bound threshold is < 60%. The upper bound threshold is ≥ 80%.

### Dichotomous acceptability of the PAS intervention

Percentage of responses observed in “yes” to the following item: “Would you recommend the online intervention to another person?” will be calculated at wave W, where W = W2. The lower bound threshold is < 60%. The upper bound threshold is ≥ 80%.

### Qualitative acceptability of the PAS intervention

Qualitative themes that emerge from a response to a qualitative item designed to assess the acceptability will be analyzed at wave W, where W = W2. The lower bound threshold is the presence of at least one potentially serious problem that is unable to be addressed in a future study. The upper bound threshold is the absence of the potentially serious problem.

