### Data analysis

Data analyses will include both quantitative and qualitative approaches. Quantitative analyses will be performed in M*plus* 8.0 under maximum-likelihood estimation with robust standard errors [62]. Missing data will be modeled under the assumption of missing at random [63]. Qualitative feedback will be summarized based on themes that emerge from the research team’s analysis. The threshold values for the traffic light system described in the feasibility outcome section will be used to evaluate results of specific indicators within each specific aim and with regard to the feasibility of a future definitive RCT. More specifically, descriptive statistics will be used to determine the feasibility of implementing the PAS intervention and the acceptability of implementing the PAS intervention. Intention-to-treat approach will be used to provide the preliminary effect size estimates [64]. The covariates, the outcome at W1, and group assignment will be specified as predictors in the approach.

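### For the two qualitative acceptability indicators, Table 2 and the text set different red-light rules, so a serious but addressable problem has no settled light

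*Protocol article*

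**What the plan says.** The section Feasibility outcomes describes a three-level system. A result below the lower threshold is red, one between the thresholds is yellow and calls for caution, and one above the upper threshold is green and supports a definitive trial. It then says: "The lower and upper bound threshold values for the traffic light system by aim are summarized in Table 2".

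For both qualitative rows, Table 2 gives "at least one potentially serious problem" as the lower bound and "absence of a potentially serious problem" as the upper bound. No footnote qualifies either cell.

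The section Qualitative acceptability of the PAS intervention gives the lower bound as "the presence of at least one potentially serious problem that is unable to be addressed in a future study". It continues: "The upper bound threshold is the absence of the potentially serious problem". The section Qualitative acceptability of accelerometer-based assessment of PA uses the same two sentences.

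Under Data analysis, the thresholds "will be used to evaluate results of specific indicators within each specific aim and with regard to the feasibility of a future definitive RCT".

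**The concern.** The text makes red depend on whether the problem can be addressed later, and Table 2 does not. The two places therefore state different decision rules for the same indicators. They part on one kind of finding: a problem that is serious but can be remedied before the next trial. That is also the finding for which a caution light seems most apt.

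The thresholds are set in advance so that the reading of each indicator is not settled after the results are seen. Here the open-ended comments are grouped into themes by the research team itself. With two published rules, the team could cite either one once the comments are known. At the extreme, the same theme could be reported as a serious warning under the table or as support for proceeding under one reading of the text.

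**Working it through.** No arithmetic applies. The check sets the rules side by side and applies them to every kind of finding.

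**Rules**

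- Table 2: red if there is any potentially serious problem; green if there is none.
- Text: red if at least one potentially serious problem cannot be addressed in a future study; green if *the* potentially serious problem is absent.

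The green rule in the text has two readings. In reading A, *the* problem is the one just defined in the preceding sentence, that is, the unaddressable one. In reading B, it is any potentially serious problem. Reading A is the more natural grammatically. Reading B agrees with the green cell of Table 2.

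**Result by type of finding**

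| Finding | Table 2 | Text, reading A | Text, reading B |
|---|---|---|---|
| No serious problem | green | green | green |
| Serious problem(s), all addressable | red | green | yellow |
| At least one serious problem that cannot be addressed | red | red | red |

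The rules agree in the first and third rows. In the second row they disagree on either reading: by two levels under A and by one level under B. The result is the same for both indicators because the text wording is the same.

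**Is yellow possible?** In Table 2, red is the presence of a serious problem and green is its absence. One or the other must hold, so yellow cannot occur. The same is true of the text under reading A. Under reading B, yellow is the serious but addressable case.

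**Is Table 2 generally looser than the text?** Table 2 has 5 rows for Aim 1, 7 for Aim 2 and 1 for Aim 3, so 5 + 7 + 1 = 13. The other 13 − 2 = 11 rows carry numerical thresholds. Each matches its text section, for example 40% and 60% for recruitment rate and 0.00 and 0.20 for the Aim 3 effect size. Each also leaves a gap between its bounds for yellow. Only the two qualitative rows differ from the text.

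**The case against.** The strongest reply is that Table 2 is offered as a summary. Its qualitative cells are then more likely shortened wording than a rival rule, and the text states the addressability condition identically in two places, which points to the intended red rule. If red is taken from the text and green from Table 2, a coherent three-level rule results, with yellow for the addressable case. This may well be what the authors meant, but it does not remove the conflict. The dropped condition changes the light, and the other 11 rows reproduce their thresholds exactly. The general definition of a red light also mentions a potentially serious problem with no condition on addressability, which fits the table better than the text. A reader has to guess which place governs.

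Two other parts of the reply stand. First, a reader might infer that the light always flips from red to green and that yellow is impossible in both places. The documents support this only under reading A; under reading B the text gives yellow. Second, a reader might suppose that a fixable problem is the result a pilot is most likely to give. The article contains nothing on that, and the point does not need it.

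It is also fair to say that the lights are advisory. They are described as suggesting a problem, caution or support, and no indicator alone stops or permits the definitive trial.

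**Conclusion.** The inconsistency is real and lies in the current text. For both qualitative indicators, a serious but addressable problem is red under Table 2 and not red under the text. The gap is two levels if the green rule in the text refers back to the unaddressable problem, and one level if it refers to any serious problem. Table 2 allows no yellow; the text allows it only on the second reading.

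The reach is limited. Both indicators are secondary within Aim 2. Participation rate, engagement behavior and the effect size for PAS on accelerometer-measured activity, which are the primary feasibility outcomes, are untouched, as are the sample size and data collection. A reader might infer that the progression decision as a whole is compromised; the article does not support that. The point is still worth correcting, because these are stated thresholds for judging the feasibility of the definitive trial.

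**What to change.** State one rule in Table 2 and repeat it in both text sections:

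- red: at least one potentially serious problem that cannot be addressed in a future study;
- yellow: at least one potentially serious problem, all of which can be addressed;
- green: no potentially serious problem.

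This keeps the text's condition for red and Table 2's condition for green, and it restores the middle level that the system defines.

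The cost is a change of wording in two table rows and two short sections, with no new data or procedures. Some results that could have been read as green under the text, or as red under Table 2, become yellow. What counts as serious or addressable remains the research team's judgment. The change narrows the discretion over the light but does not remove it.

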### Quantitative acceptability of accelerometer-based assessment of PA

Percentage of responses observed in “agree” or “strongly agree” to each of the four Likert-scale items designed to assess the acceptability of accelerometer-based assessment of PA will be calculated at wave W, where W = W1 or W3. The lower bound threshold is < 60%. The upper bound threshold is ≥ 80%.

### Dichotomous acceptability of accelerometer-based assessment of PA

Percentage of responses observed in “yes” to the following item: “Would you be willing to wear the monitor again as part of a new research study?” will be calculated at wave W, where W = W1 or W3. The lower bound threshold is < 60%. The upper bound threshold is ≥ 80%.

### Qualitative acceptability of accelerometer-based assessment of PA

Qualitative themes that emerge from a response to qualitative items designed to assess the acceptability will be analyzed at wave W, where W = W1 or W3. The lower bound threshold is the presence of at least one potentially serious problem that is unable to be addressed in a future study. The upper bound threshold is the absence of the potentially serious problem.

### Aim 3

The Aim 3 is to provide a preliminary effect size estimate for each direct effect depicted in the conceptual model (see Fig. 1) for the PAS intervention. The preliminary effect size estimate for the direct effect of PAS to accelerometer-based assessment of PA will be the primary outcome in Aim 3. There will be secondary feasibility outcomes (e.g., PAS self-efficacy, self-efficacy PA) in Aim 3. The secondary feasibility outcomes in Aim 3 may provide additional information regarding the mechanism of the PAS intervention aimed at promoting PA. The preliminary effect sizes for each direct effect of being assigned to the PAS intervention at wave W, where W = W2 or W3 will be estimated. The lower bound threshold is < 0.00. The upper bound threshold is ≥ 0.20.

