### Recruitment

Thirty participants will be recruited in this study. Patients who are enrolling in the weight management program provided by the center will be potential participants in the study (e.g., ~ 70 potential participants). They will be asked to consider their participation in this study by a research staff member who is affiliated with the center via in-person communication or remote communication. The research staff will provide only those interested in the study (e.g., ≤ 70 potential participants) with login information to the secure recruitment page on the PAS website which can then be accessed via their own device (e.g., smartphone). The PAS website will automatically stop recruitment once 30 participants provide their remote consent forms. We expect that the recruitment may take about one month.

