### Sample size

The sample size (i.e., 30 participants) is based on the primary feasibility outcomes (see the feasibility outcome section for detailed information), the budgetary constraints, and the range of sample sizes observed in pilot and feasibility trials. Thirty participants may provide some data to use descriptive statistics for the primary feasibility outcomes (i.e., participation rate in Aim 1, engagement behavior in Aim 2). If the recruitment rate is 50% in this study, the targeted sample size can be used because the center usually has approximately 70 patients enrolled in their program. Budgetary constraints preclude enrollment of more than 30 participants in this study. Also, the targeted number of participants may provide some data about the preliminary effect size estimate for the direct effect of PAS to PA. The sample size in a feasibility study is not based on a sample size determination for a desired level of statistical power [42–44]. The target sample size in this study fits within the range of sample sizes often observed in pilot and feasibility trials [45].

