### Randomization

Thirty participants will be randomly assigned to the PAS group or the Usual Care (UC) group to achieve a 1:1 group assignment. The randomization will be performed by the PAS intervention website (i.e., computer-generated random numbers). Neither participants nor the research staff will know which group a participant will be assigned into.

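### The Aim 3 traffic light is set by the point estimate of the effect on physical activity alone, and with 30 participants it cannot separate the small effects that its own cut-offs are meant to separate

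*Protocol article*

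**What the plan says.** The section on feasibility outcomes lists three primary outcomes. The third is "a preliminary effect size estimate for the direct effect of PAS to accelerometer-based assessment of PA (i.e., Aim 3"). The Aim 3 paragraph and the Aim 3 row of Table 2 set its cut-offs: "The lower bound threshold is < 0.00. The upper bound threshold is ≥ 0.20". The scale is Cohen's d, since the section refers to customary benchmarks for that measure.

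The same section explains the lights. A value below the lower cut-off points to a possibly serious problem, and a value between the cut-offs calls for caution. At the top, "Data observed above an upper threshold (i.e., resembling green light) will suggest support for the feasibility of a future definitive" RCT. The Data analysis section then applies the cut-offs both to each indicator and to the feasibility of the future RCT. It fits the effect model by intention to treat, with the covariates, the W1 outcome and group as predictors.

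On size, "Thirty participants will be randomly assigned to the PAS group or the Usual Care (UC) group to achieve a 1:1 group assignment". The Sample size section states that "The sample size in a feasibility study is not based on a sample size determination for a desired level of statistical power" and that "the targeted number of participants may provide some data about the preliminary effect size estimate for the direct effect of PAS to PA". No interval or other allowance for sampling error is attached to the Aim 3 light.

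**The concern.** The rule sorts an estimate into three classes whose boundaries are 0.20 standard deviations apart. That is informative only if the estimate is precise on that scale. The Sample size section claims no such precision, yet the result still receives a light that bears on the definitive trial.

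Two errors matter. An intervention with no effect on activity may be reported as supporting a definitive RCT. An intervention with exactly the effect that the plan treats as supportive may be reported as having a possibly serious problem. If either is common, the Aim 3 light adds noise to the progression judgement while appearing as a primary result.

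**Working it through.** The plan gives no power or precision figure for Aim 3, so there is none to reproduce. The check is how often each light appears for a given true effect.

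**Inputs from the protocol article**
- 30 participants, allocated 1:1, so 15 per arm (Recruitment; Randomization).
- Red below 0.00, yellow from 0.00 to below 0.20, green at 0.20 or above (Aim 3; Table 2).
- Adjustment for the W1 outcome (Data analysis).
- Participation is green from 70% (Participation rate): 0.70 × 30 = 21 usable, or 10.5 per arm if split evenly.

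**Assumptions, not in the article**
- W1–W3 correlation r from 0 to 0.7.
- A range of true effects d.
- d standardised by the unadjusted standard deviation.
- An approximately normal estimate.

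**Formulas**
- SE(d) = √[(2/n)(1 − r²)], with n per arm
- P(red) = Φ((0 − d)/SE)
- P(green) = 1 − Φ((0.20 − d)/SE)

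**Precision with 30 usable**
- r = 0: √(2/15) = 0.365; 95% half-width 1.96 × 0.365 = 0.72.
- r = 0.7: √(0.1333 × 0.51) = 0.261; half-width 1.96 × 0.261 = 0.51.

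The yellow band is therefore only 0.20/0.365 = 0.55 standard errors wide at r = 0, and 0.20/0.261 = 0.77 at r = 0.7.

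**Precision with 21 usable**
- r = 0: √(2/10.5) = 0.436.
- r = 0.7: √(0.1905 × 0.51) = 0.312.

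**The two errors.** P(green) at d = 0 equals P(red) at d = 0.20, by symmetry. Both are 1 − Φ(0.20/SE).

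| Usable | r | SE | 0.20/SE | Probability of either error |
|---|---|---|---|---|
| 30 | 0.7 | 0.261 | 0.77 | 22% |
| 30 | 0 | 0.365 | 0.55 | 29% |
| 21 | 0.7 | 0.312 | 0.64 | 26% |
| 21 | 0 | 0.436 | 0.46 | 32% |

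**Across true effects, 30 usable, r = 0**

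| True d | Red | Yellow | Green |
|---|---|---|---|
| 0 | 50% | 21% | 29% |
| 0.20 | 29% | 21% | 50% |
| 0.30 | 21% | 19% | 61% |
| 0.50 | 9% | 12% | 79% |
| 0.80 | 1% | 4% | 95% |

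Rows may not add to 100% because of rounding. At r = 0.7, a true d of 0.50 gives 88% green and 3% red. A noncentral t calculation for 15 per arm, unadjusted, agrees within 0.003.

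**Scale.** To hold both errors at 10%, these cut-offs need n = 2(1 − r²)(1.2816/0.20)² per arm. This is 82.1, so 83, at r = 0, and 41.9, so 42, at r = 0.7.

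**The case against.** The strongest reply is that this is a feasibility study and says so. Its size is openly not based on power, and the effect estimate is called preliminary throughout. The lights only suggest, and the Aim 3 row is one of 13 in Table 2. All of this is correct. A reader might infer a go/no-go rule, but the article does not write one: no red stops the RCT and no green triggers it. Nor does the point say that 30 is too few for a feasibility study. The 83 and 42 per arm above show only what this light would require.

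A reader might also infer that the light is little better than chance in general. That does not hold. The weakness is confined to small true effects, about 0 to 0.3. For d of 0.5 or more the light usually falls on the right side.

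The 50% chance of green at a true d of 0.20 should not be held against the sample size. An unbiased estimate compared with a cut-off equal to its true value passes about half the time at any size.

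It is also fair that the planned analysis is adjusted, so the unadjusted figures are one end of a range. The analysis will produce standard errors, and a fuller document may report intervals. An interval printed beside the light would not change how the light is set, however. The article fixes that on the observed value in the text and in Table 2, and applies it to RCT feasibility in the Data analysis section. Nothing there gives this primary outcome less weight than the others.

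**Conclusion.** The point holds for small effects, which are the ones that cut-offs of 0.00 and 0.20 are meant to tell apart. A null intervention would be shown as supporting the RCT, and one with an effect of 0.20 would be flagged as a possible serious problem. Each happens in about 22–29% of trials with 30 usable participants and about 26–32% with 21, a level that the plan itself rates as good participation.

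The figures rest on an assumed W1–W3 correlation of 0 to 0.7, an even split of usable data and a normal approximation. The conclusion is the same throughout that range.

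This is a badly fixed rule that should be corrected. It does not threaten the validity of the trial, and the light can misdirect the RCT decision without determining it.

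**What to change.** Remove the Aim 3 row from the traffic-light rule in Table 2 and the cut-offs from the Aim 3 paragraph. Alternatively, keep them and state that the Aim 3 light does not inform progression. Amend the Data analysis section to match. Report the adjusted wave 3 difference in MVPA (minutes per day) and d, each with a 95% confidence interval, as descriptive results. Carry the standard deviation and the W1–W3 correlation forward to plan the RCT. Base the progression judgement on the Aim 1 and Aim 2 indicators.

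An interval-based light is not a useful substitute. Turning red only when the upper 95% limit lies below 0.20 would need an observed d below about 0.20 − 0.72 = −0.52 (15 per arm, unadjusted). That happens in about 8% of trials at a true d of 0 and 2.5% at 0.20. With no green on the point estimate alone, nearly every result would be yellow.

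Sample size, visits, measures and model stay as they are. The cost is that a declared primary outcome no longer has a progression criterion, and the conclusion on Aim 3 is less decisive.
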